### The Gabby System: an evidence-based preconception care intervention

Health information technology (HIT) is an important tool for information sharing, enhancing consumer engagement, and facilitating shared decision making to improve the quality and efficiency of care [20, 21]. HIT can be leveraged to develop culturally tailored, low cost, and convenient interventions to better reach and reduce disparities in health outcomes for socially disadvantaged, underserved and health disparity populations [22]. Technology-based interventions (e.g. mHealth, eHealth) can be leveraged to enhance patient engagement, support decision making, and improve patient-provider communication. The Gabby System, here forth Gabby, is a HIT intervention programmed to screen for PCC-related risk factors and identify health and social care needs across several domains including: genetic health history; immunizations and vaccinations; sexual and reproductive health; infectious disease; health conditions and medication use; alcohol, tobacco and other drug use; social and emotional well-being; relationships and relational health; healthcare access and affordability; social determinants of health; nutrition and physical activity; and environmental wellness [18]. Gabby is an Embodied Conversational Agent (ECA) that provides comprehensive health promotion and education for each domain, assesses one’s readiness for behavior change, and tailors behavior modification strategies to the user’s risk-specific stages of change [19]. Using conversational speaking style, ECA’s are designed to emulate expert communication skills by focusing on the most salient information, evaluating the patient’s level of understanding, and repeating or elaborating information as necessary [23–25]. ECA’s use speech, gaze, hand gestures, intonation, and other nonverbal modalities to capture the experience of human face-to-face conversation with the end user. Gabby is theoretically grounded in Prochaska and DiClemente’s Transtheoretical Model [26] and uses a variety of health education and motivational strategies to support users’ progression through pre-contemplation, contemplation, preparation, action and maintenance stages of change - thus demonstrating that health behavior change is a process rather than a singular event. Users create an individualized “My Health To-Do List” (MHTDL) that they can work on at their own pace and/or discuss with their healthcare provider. Specifically designed and informed by Black and African American women, [27] the efficacy of Gabby has been demonstrated in two randomized controlled trials, and has successfully identified and resolved health risks for these women [18, 19]. While Gabby has shown strong evidence to support health behavior change in the research setting, the capacity to which these outcomes translate into the daily lives of Black and African American women and in community-based clinical contexts has yet to be determined. Utilizing HIT as an implementation modality has the potential to increase scalability, improve fidelity of information and reduce staff training time.

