## Methods

We will conduct a hybrid type II implementation-effectiveness cohort study in six Healthy Start programs and six Community Health Centers across the U.S. This study has been reviewed and approved by the Boston University Medical Center Institutional Review Board with the following designations: Not Human Subjects Research for Implementation (H-36816) and Exempt for key informant interviews (H-36716).

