To assess the effectiveness of Gabby, we will measure the rate of risk behaviors per subject at action and maintenance. Stage of change data will be collected at the initial assessment, at 3 months, and again at 5.5 months, and then compared across the three data collection points for triggered risks. We anticipate that subjects receiving an effective Gabby intervention should see a greater number of risk behaviors, from baseline to 3 and then 5.5 months, that have reached the action or maintenance stage of change. We will also assess the rate of risk behaviors per subject progressing forward on the stage of change scale. We will test for the effectiveness of Gabby by using a Poisson model to regress our stage of change rate outcomes on data collection time point, with site fixed effects. In addition, for each risk, a logistic regression model will be used to regress a binary measure of whether that risk had either remained at the action or maintenance stage or progressed forward, data collection time point, with site fixed effects.

Finally, we will run analyses to determine whether Gabby was differentially effective conditional on baseline stage of change. This will be done by restricting the data only to risks that were reported at “pre-contemplation” at baseline; then by calculating the rate that remained at “action” or “maintenance” or progressed forward, and finally by regressing that rate on the period of data collection using a Poisson model with site fixed effects. This procedure will be repeated by restricting the data to risks reported at “contemplation” at baseline, and again by restricting risks reported at “preparation” and then “action” stages of change. All statistical tests will be run at alpha level a = 0.05 and performed using the R programming language, version 3.4.3 [45].

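### The baseline-stage analysis sets out to find differential effectiveness, but its four separate models never compare the stages, and its outcome rule fixes the baseline value in each stratum

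*Protocol article*

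**What the plan says.** The last analysis in the protocol article's Quantitative analysis section has an inferential aim: "we will run analyses to determine whether Gabby was differentially effective conditional on baseline stage of change". The method starts with one stratum, pre-contemplation: "This will be done by restricting the data only to risks that were reported at" that stage. The rate of success among those risks is then calculated, and the model step is described as "regressing that rate on the period of data collection using a Poisson model with site fixed effects". The same steps are then applied in turn to risks that began at contemplation, preparation and action. That makes four fits. Maintenance at baseline is not listed.

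Success is defined as in the preceding per-risk logistic model: "whether that risk had either remained at the action or maintenance stage or progressed forward". On timing, "Stage of change data will be collected at the initial assessment, at 3 months, and again at 5.5 months", and the section says that stages are compared across these three points. Every test is run at an alpha of 0.05.

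The design has no control group. The Methods section says "We will conduct a hybrid type II implementation-effectiveness cohort study". The scale is ordered and bounded at both ends; the section on the Gabby System describes "progression through pre-contemplation, contemplation, preparation, action and maintenance stages of change".

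**The concern.** A claim of differential effectiveness is a claim about a difference between strata. Each planned model estimates change over time within one stratum and has no stage term, so no stated analysis estimates or tests that difference.

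The outcome has one wording but does not mean the same thing in each stratum. Staying put is a failure for a risk that starts at pre-contemplation, contemplation or preparation, and a success for one that starts at action. A pre-contemplation risk cannot move back. An action risk has one step left above it. Some contrast between strata is therefore built into the scoring.

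The strata are also selected on the baseline value of the same self-reported scale that supplies the outcome, with no comparator. Regression to the mean can therefore add to differences between strata in follow-up success levels.

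At stake is a published statement that Gabby works better or worse according to readiness to change, resting on an analysis that cannot support it.

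**Working it through.** **The plan's own figures.** The protocol gives no number for this analysis. Its only sample-size figure, at least 125 subjects, is for the overall paired change. Reading the stated 28.7% as a standard deviation, (1.960 + 0.842)² × (28.7 / 7.3)² = 121.3, or 124 with the noncentral t. The 125 therefore reproduces, but it says nothing about the strata.

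**Step 1: the outcome rule applied at baseline.** This needs only the rule and the stage order.

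| Baseline stage | Outcome at baseline | Holding still later counts as | Possible change from baseline |
|---|---|---|---|
| Pre-contemplation | 0% | failure | up or none |
| Contemplation | 0% | failure | up or none |
| Preparation | 0% | failure | up or none |
| Action | 100% | success | down or none |

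The first three are 0% because such a risk is neither at action or maintenance nor, yet, any further forward. The fourth is 100% because it is at action.

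**Step 2: the two readings of period.** The section does not say whether baseline is one of the periods in these models.

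- Baseline included: the direction of the period effect is fixed by the table. If period is a category with baseline as reference, the baseline log rate in the first three strata is log(0), which is undefined.
- Baseline excluded: the only contrast is 3 against 5.5 months. Movement between baseline and 3 months does not enter the period effect.

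**Step 3: the missing comparison.** Suppose that all four strata have the same true effect and each test has power p. With independent tests, the chance that the four verdicts are not all alike is 1 − p⁴ − (1 − p)⁴.

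- p = 0.80: 1 − 0.4096 − 0.0016 = 0.589.
- p = 0.50: 1 − 0.0625 − 0.0625 = 0.875.

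The power values are illustrative. One woman can have risks in several strata, so the tests are unlikely to be independent; positive dependence would lower both figures.

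**Step 4: regression to the mean.** Two simulations with no net change were run, using inputs that the documents do not supply. In the first, true stage is stable and each report is one stage off with total probability 0.1 to 0.3, under three assumed stage distributions. In the second, a latent normal scale is cut into five equal stages with test-retest correlation 0.6 to 0.9. Success at follow-up was:

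| Baseline stage | Reporting-error model | Latent-correlation model |
|---|---|---|
| Pre-contemplation | 9–36% | 25–51% |
| Contemplation | 8–27% | 32–47% |
| Preparation | 8–23% | 29–38% |
| Action | 73–91% | 53–69% |

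Both models put action above the other strata with no net change, largely because holding still counts as success there. For contemplation, preparation and action the two sets of ranges do not overlap, so the size depends on the assumptions. These are levels at one follow-up, not period effects. Under either model, if the same error or correlation applies at 3 and 5.5 months, the expected change between those two points is zero in every stratum.

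**The case against.** The strongest reply is that the models test a period effect, and that an outcome about remaining or progressing is naturally defined only after baseline. On that reading, movement due to stable reporting error has already happened by 3 months and adds nothing to the contrast with 5.5 months. This is right, and it limits the role of regression to the mean. It does not rescue the analysis, which then leaves out the change from baseline and still makes no comparison between stages.

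A second reply is that stratum rate ratios with intervals could be set side by side, and that nothing in the text says p-values will be compared. That is fair: reading the strata by significance is an inference. But the section specifies only within-stratum tests, and no comparison of any kind.

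Third, this is the last-listed analysis and the sample size does not rest on it. That stands. The main effectiveness analysis is unaffected.

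A reader might go further and infer that selection on baseline guarantees a spurious stage pattern in the fitted models, or that all apparent movement would be measurement noise. The documents support neither. They give no reliability and no stage distribution, and a test-retest correlation cannot separate reporting error from real individual change over months. A reader might also infer that the results would decide which women the sites approach. No section says so, and the eligibility criteria do not mention stage.

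**Conclusion.** The concern holds as a defect in a stated method. Two parts follow from the text alone: no analysis compares the strata, and the outcome is 0% at baseline in three strata and 100% in the fourth. With baseline included, the direction of the period effect is therefore settled in advance; with baseline excluded, change from baseline is missed. Neither reading answers the question posed.

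The 59% disagreement figure assumes equal true effects, 80% power in each stratum and independent tests. Regression to the mean is a possible further contributor to differences in follow-up levels, of a size the documents do not allow one to state. As planned, the analysis can describe movement by baseline stage but cannot establish differential effectiveness. It should be changed, though the main effectiveness result does not depend on it.

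**What to change.** Replace the four fits with one model of follow-up stage at 3 and 5.5 months on all triggered risks. Include baseline stage, time, their interaction and site, and allow for several risks and repeated measurements within a woman. State whether risks at maintenance at baseline are included. Test the between-stage comparison once, through the interaction.

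Report the full table of baseline stage against stage at each follow-up. It shows movement from baseline, including backward moves, without a success rule that differs in meaning by stratum.

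Describe the results as movement by baseline stage, not as differential effectiveness. The interaction supplies the missing comparison, but without a comparator it does not remove floor, ceiling or regression to the mean. If stage-specific control-arm data from the sponsor's earlier randomised trial prove available, they could serve as an external comparison; the protocol does not say that they are, and that trial recruited nationally, not through these sites.

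The change is to analysis and reporting text and needs no new data collection. The price is a weaker permitted conclusion from this analysis.

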### Sample size and power calculation

To assess implementation based on usage and uptake, we will treat the sample size calculated for effectiveness as a convenience sample. Because usage and uptake are being analyzed descriptively with no baseline data and no over-time comparison, it is not appropriate to calculate power for these outcomes.

To assess effectiveness based on per-end-user stage of change outcomes, our target sample size calculation is based on 12 available sites. Based on our previous RCT of 528 African American/Black women recruited nationally, [19] we expect to see an approximately 7.3% difference in the rate of risks behaviors achieving action or maintenance from 0 to 5.5 months, with a common error variance of approximately 28.7%. With paired two-sided tests, at a power of 0.80 and a significance level of 0.05, we would require at least 125 subjects to detect an effect of at least this magnitude. Because end-users are nested within sites, we also must account for within-site clustering. Based on published intra-class correlation coefficient (ICC) data from 61 clinical practices in 8 practice based research networks on risks such as smoking, diet, and exercise, we anticipate an ICC of 0.012 and a design effect of 1.3 [33]. Based on this design effect, we require at least 160 end-users, or 13 end-users per site. If we anticipate only about 2/3 of end-users to provide outcome data (consistent with our previous study), then we must enroll approximately 240 users, or 20 end-users per site, to detect a change in our outcome from 0 to 5.5 months.

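### Every effectiveness test runs at an unadjusted 0.05 and the only powered contrast is not named as the primary test, so the familywise error for aim 2 is uncontrolled and well above 5%

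*Protocol article*

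**What the plan says.** Aims and objectives makes effectiveness one of two co-primary aims. The Quantitative analysis section tests it in three layers:

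- Poisson models for two rate outcomes per woman, compared across baseline, 3 and 5.5 months: risks at action or maintenance, and risks that moved forward in stage.
- Per-risk models: "for each risk, a logistic regression model will be used", again regressed on time point.
- Four further Poisson models, each restricted to risks that began at one baseline stage (pre-contemplation, contemplation, preparation, action).

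The section closes with one rule for all of them: "All statistical tests will be run at alpha level a = 0.05". It gives no adjustment, no testing order, and no label of primary, secondary or exploratory for any test.

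The Sample size and power calculation section is narrower. It sizes the study on one outcome and one interval: "we expect to see an approximately 7.3% difference in the rate of risks behaviors achieving action or maintenance from 0 to 5.5 months".

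**The concern.** The sizing section commits to one question, while the analysis section asks many and holds each to the same threshold. It says that both rate outcomes serve to test effectiveness, and it ranks neither 3 nor 5.5 months above the other. Quantitative data collection and measures describes risk resolution in a third way, risk by risk at both follow-up times, so a reader could take the per-risk results as the main evidence.

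At stake is what a positive result would mean. If the powered contrast were null but a few single risks, or the 3-month comparison, fell below 0.05, nothing in the plan says how aim 2 should be judged. Isolated per-risk findings would also be reported with no allowance for how many risks were examined.

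**Working it through.** **1. The plan's own sample size.** The inputs come from Sample size and power calculation: difference 0.073, variability 0.287, two-sided alpha 0.05, power 0.80.

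- Paired test: n = ((1.960 + 0.842) × 0.287 / 0.073)² = 121.3, so 122. The paired t version gives 124, and power at 125 is 0.806. The plan states: "With paired two-sided tests, at a power of 0.80 and a significance level of 0.05, we would require at least 125 subjects". This reproduces when 28.7% is used as the standard deviation of the paired difference.
- Design effect: 125 × 1.3 = 162.5, against the stated 160.
- Attrition: 160 / (2/3) = 240, and 240 / 12 = 20 per site.

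The study is thus sized for one test at 0.05.

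**2. Number of effectiveness tests.** There are 2 rate outcomes, 4 baseline-stage models and R per-risk models. R is not stated. The section describing the Gabby System lists 12 domains, so R = 12 is taken as an assumption, with 50 and 100 shown as a range.

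- One test per model (for example, a joint test of time): 2 + 4 + 12 = 18.
- Two contrasts with baseline per model (3 and 5.5 months): 2 × 18 = 36.

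**3. Chance of at least one false positive when there is no effect.** Under independence this is 1 − 0.95^K for an error in either direction. For errors favouring the intervention it is 1 − 0.975^K, because half of a two-sided 0.05 lies on that side.

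- K = 18: 1 − 0.95^18 = 60%; favourable only, 1 − 0.975^18 = 37%.
- K = 36: 1 − 0.95^36 = 84%; favourable only, 1 − 0.975^36 = 60%.

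The tests share the same women, so they are correlated. The correlated columns come from a simulation of equally correlated normal test statistics with 40,000 draws. Figures in brackets count favourable errors only.

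| Tests (K) | Independent | Correlation 0.3 | Correlation 0.5 |
|---|---|---|---|
| 18 (12 risks, one test per model) | 60% (37%) | 51% (27%) | 40% (20%) |
| 36 (12 risks, two contrasts per model) | 84% (60%) | 71% (38%) | 55% (28%) |
| 56 (50 risks, one test per model) | 94% (76%) | 83% (47%) | 65% (33%) |
| 106 (100 risks, one test per model) | 99.6% (93%) | 95% (59%) | 79% (41%) |

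For one prespecified test the corresponding figures are 5% (2.5%).

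**4. What each remedy does to power.** With the powered contrast as the single primary test, its error is 0.05 and 125/160/240 stand. Bonferroni over all 18 tests would use 0.05 / 18 = 0.0028 per test. The paired n would rise from 122 to 228, and power at n = 125 would fall to about 0.44.

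**The case against.** The strongest reply is that the primary test can be inferred. Effectiveness is sized on one outcome and interval, the analysis section opens with that outcome, and the others are introduced as additions. The baseline-stage models ask whether the effect differs by starting stage, and the per-risk models can be read as descriptive detail. Labels and adjustment procedures are often left to a statistical analysis plan, and one may exist here.

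Part of this stands. The order of presentation does point to action/maintenance as the lead outcome. It does not settle the time contrast, since 3 and 5.5 months are given equal standing, and both rate outcomes are said to test effectiveness. Nor is the article silent on alpha. It states a rule for every test, which a later plan would have to override.

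The count is also open to challenge. Regressing on time point allows one joint test per model. Progression is defined relative to baseline, so it may have no baseline value to compare with. That is why 18 tests, and not 36, carries the conclusion here.

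A reader might go further and infer that a false claim of effectiveness is close to certain. The document does not support that. With independent tests a 95% chance needs 59 tests, or 119 if only favourable errors count. The number of risks is unknown and correlation lowers the figures. The text also nowhere says that one significant result would prove effectiveness.

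A reader might likewise infer that the per-risk models will fail through sparse data within sites. That depends on how often each risk is triggered, which the document does not give, so it is not claimed.

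**Conclusion.** The point holds. As written, the plan leaves the familywise error for aim 2 uncontrolled and well above 5%. At 12 risks and one test per model, at least one false positive has a chance of about 60% under independence and 40% to 51% at correlations of 0.5 to 0.3. For a false favourable result the range is about 20% to 37%, against 2.5% for a single test. With two independent contrasts per model the any-error figure is 84%, and more risks raise it further. These figures rest on the assumed number of risks, the number of tests per model and the correlation. That the error exceeds 5% does not depend on the exact choice: the two rate outcomes, each at two follow-up times, already give 1 − 0.95^4 = 18.5% under independence. The powered contrast itself is sound as a 0.05 test; what is missing is its designation as the test that decides aim 2.

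**What to change.** In Quantitative analysis:

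- Name the change in the action/maintenance rate from 0 to 5.5 months as the single primary test of aim 2, at two-sided 0.05.
- Label the 3-month comparison, the progression outcome, the per-risk models and the baseline-stage models secondary or exploratory.
- Control the false discovery rate across the per-risk models (Benjamini-Hochberg, 5%), and state how many risks are in that family.
- Limit the blanket alpha sentence accordingly.

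All planned analyses remain and the sample size of 125/160/240 is unchanged. The cost is a few sentences and a routine adjustment. The downside is that some single-risk results will lose significance. Bonferroni across every test is not advised, given the loss of power shown above.
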